### Interim analysis

The external trial board will execute the interim analysis after half of the patients have been recruited. The analysis will focus on the number of adverse events and the trial board, based on the results of the analysis, will give a recommendation as to whether the trial should continue. If complications rate in accelerated rehabilitation group is remarkably increased in that phase, the study is discarded. Adverse events and serious adverse events will be reported according to the recommendations given by the Consort Group. They will be reported as complications in the final analysis.

Adverse event is defined as follows:

➢ Superficial infection➢ Persisting pain, complex regional pain syndrome or other reasons that can be cured on an ambulatory basis.

Serious adverse event is defined as follows:

➢ Deep infection: Any infection with known bacterial source that calls for re-operation➢ Implant failure leading to displacement of the osteotomy➢ Non-union at 12 weeks control visit

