** Assessments **						
BPII score	x		x	x	x	x
KOOS	x		x	x	x	x
Adverse events		x	x	x	x	x

TT-distalisation–distalisation of tibial tubercle; BPII–Banff Patella Instability Instrument; KOOS–Knee Injury and Osteoarthritis Outcome Score.

The hypothesis of the trial is that the novel accelerated rehabilitation protocol will lead to faster recovery and improved functional outcome at 6, 12 and 24 weeks compared with the conservative rehabilitation protocol. The secondary hypothesis is that the complication rate will be similar for both protocols.

The primary outcome in this study will be knee ROM measured at 12 weeks postoperatively. A total difference regardless of the direction of the movement of 10° in full range of movement will be considered significant. The results will be measured with a long goniometer in a standardised manner. Secondary outcomes will be knee ROM measured at baseline, 6, 24 and 52 weeks postoperatively, the Knee Injury and Osteoarthritis Outcome Score (KOOS) and the Banff Patella Instability Instrument (BPII) score measured at baseline, 6, 12, 24 and 52 weeks, and isometric muscle strength measured at baseline, 12, 24 and 52 weeks postoperatively. Regained isometric muscle strength will be measured during follow-up visits and calculated to a ratio compared with a preoperative value. The number of reoperations and complications (failure of fixation and stress-fractures) will be also reported as secondary outcomes. The KOOS questionnaire is an instrument to assess patients’ opinions about their knees and any associated problems. KOOS consists of 5 subscales: Pain, other Symptoms, Function in daily living, Function in sport and recreation and knee related Quality of life. BPII is also a patient-reported outcome measurement instrument. BPII is, however, more specific for patellofemoral problems.

After enrolment, all the patients visit the study physiotherapist. The baseline scores from ROM, isometric muscle strength, KOOS and BPII are recorded during the visit. Randomisation to the allocation groups will be done after surgery.

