### Patient selection

The eligible study population will comprise all consecutive patients aged 15 to 35 years with closed growth plate (physis) who have been referred for DTTO surgery at Pihlajalinna Koskisairaala Hospital, Tampere, Finland. The upper age limit was chosen to minimize the effect of patellofemoral osteoarthritis. As the DTTO procedure can only be planned for skeletally mature patients, the closure of the physis will be evaluated with magnetic resonance imaging (MRI) and plain radiographs. The Greulich and Pyle method will be used to define skeletal age if needed [7].

Only those patients with isolated DTTO or DTTO combined with medial patellofemoral ligament reconstruction will be included in the study. At the initial out-patient ward the treating physician will give the information about the study and ask for written informed consent.

The following criteria will be used for patient selection throughout the study.

❖ Inclusion criteriaSymptomatic patella alta with recurrent dislocation or subluxation. Long-lasting anterior knee pain not responding to rehabilitation.❖ Exclusion criteria➢ Radiographic:Open growth platesIwano [8] grade III and IV changes in patellofemoral jointCaton-Deschamps <1.2 in MRIPTI >30% in MRIHigh grade trochlear dysplasia➢ General:Refuses to participate in the studyAged less than 15 or more than 35 yearsSevere neurological, pulmonal or cardiovascular comorbidities that are contraindications for surgeryLack of adequate co-operationDoes not adequately understand written and spoken instructions in the local language

Those patients who decline to take part in the trial will be asked to join a follow-up cohort as a background population. The patients in this follow-up cohort will be treated “as normal” without allocation, but the follow-up questionnaires will be the same as those given to the randomly assigned population. The patients in the follow-up cohort will also be asked to provide informed written consent.

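### Persisting pain counts as an adverse event with no preoperative reference although pain is an entry criterion, and the article gives two conflicting definitions of a complication

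*Protocol article*

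**What the plan says.** All references are to the protocol article.

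- **Patient selection** lists among the inclusion criteria "Long-lasting anterior knee pain not responding to rehabilitation". The Introduction names patellofemoral pain as a possible symptom of patella alta, with or without instability.
- **Interim analysis** defines as an adverse event "Persisting pain, complex regional pain syndrome or other reasons that can be cured on an ambulatory basis". It gives no onset, severity or change from baseline. Of adverse and serious adverse events it says "They will be reported as complications in the final analysis".
- The same section says of the interim look: "The analysis will focus on the number of adverse events". On the consequence it says: "If complications rate in accelerated rehabilitation group is remarkably increased in that phase, the study is discarded". Serious adverse events form a separate list without pain: deep infection, implant failure with displacement, and non-union at 12 weeks.
- **Materials and methods** (text after Table 1) uses another definition: "The number of reoperations and complications (failure of fixation and stress-fractures) will be also reported as secondary outcomes". The hypothesis stands just before it: "The secondary hypothesis is that the complication rate will be similar for both protocols".
- **Statistical analysis** plans an adjusted risk difference at each time point for complications and reoperations.

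**The concern.** A patient who enters with long-standing knee pain and still has some of it after surgery fits the adverse event wording as it stands, whichever rehabilitation was allocated. Such an event may reflect the underlying condition or an incomplete surgical result, and then says little about the rehabilitation protocol.

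Two things are at stake. The first is the secondary hypothesis of similar complication rates. A background event common to both arms shrinks the observed difference and makes it noisier. If similarity is read from a small or non-significant difference, both effects favour the trial's own hypothesis. The second is clarity. With two definitions in one article, two complication rates could be computed from the same data, and the article does not say which one tests the hypothesis.

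**Working it through.** **The plan's own figure.** The article sizes the trial on range of motion only: difference 10°, SD 20°, 80% power, 5% type I error. Per group, n = 2(1.96 + 0.8416)² × (20/10)² = 62.8, so 63, as stated. Allowing for 5% loss, 126 × 1.05 = 132.3, in line with the stated 132. None of this is in dispute. The article states no complication rate and no pain rate, so every rate below is an assumption.

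**Set-up.** Let p be the rate of structural and serious events and b the rate of unresolved entry pain among all randomised patients, equal and independent in both arms. If one any-event rate is formed:

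- Rate in an arm: q = 1 − (1 − p)(1 − b).
- Risk difference: q_acc − q_con = (p_acc − p_con)(1 − b).
- z = difference / √[(q_con(1 − q_con) + q_acc(1 − q_acc))/n]; power ≈ 1 − Φ(1.96 − z).

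**Numbers**, with assumed p of 3% (conservative) and 12% (accelerated), and n = 63 per arm:

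| b | q conservative | q accelerated | Difference (points) | z | Power |
|---|---|---|---|---|---|
| 0 | 3.0% | 12.0% | 9.0 | 1.95 | 49% |
| 15% | 1 − 0.97 × 0.85 = 17.55% | 1 − 0.88 × 0.85 = 25.2% | 7.65 | 1.05 | 18% |
| 30% | 1 − 0.97 × 0.70 = 32.1% | 1 − 0.88 × 0.70 = 38.4% | 6.3 | 0.74 | 11% |

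For example, at b = 15%: √[(0.1755 × 0.8245 + 0.252 × 0.748)/63] = 0.0727, and 0.0765/0.0727 = 1.05.

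**Other assumed rates.** With 5% v 20% and b = 20%, the difference falls from 15.0 to 12.0 points. Power at 63 per arm falls from 73% to 31% (pooled-variance formula), or from 66% to 25% by Fisher's exact test. With 3% v 15% and b = 40%, the difference falls from 12.0 to 7.2 points. The direction is the same throughout; the size depends on the assumptions.

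**Interim look.** The section says "The external trial board will execute the interim analysis after half of the patients have been recruited". That is 66 of 132, about 33 per arm. On the 3% v 12% rates, z for a single any-event rate is 1.41 without pain, 0.76 at b = 15% and 0.54 at b = 30%.

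**If pain differs by arm.** Keep 3% v 12% and pain of 15% in the conservative arm. With 20% pain in the accelerated arm the difference is 0.97 × 0.85 − 0.88 × 0.80 = 0.1205, or 12.05 points. With 10% it is 0.8245 − 0.88 × 0.90 = 0.0325, or 3.25 points. Against the 9.0 points without pain, the distortion can go up or down.

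**The case against.** The strongest counter-argument is that the outcome definition in Materials and methods contains no pain. It stands beside the secondary hypothesis, and the Statistical analysis section's pairing of complications with reoperations matches it. On that reading persisting pain never enters the similarity comparison. This is a fair reading and it limits the point: dilution of the secondary hypothesis is conditional. It does not remove the point, because the Interim analysis section says that adverse events are reported as complications in the final analysis.

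Four stronger readings are tempting, and the article does not support them:

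- *All events are pooled into one rate.* The section keeps two lists and never states a single any-event rate. The arithmetic above applies only if one is formed.
- *The interim look will miss fixation failures.* No test or threshold is given, the board is external, and serious events are defined separately. A board that sees them on their own is not shown to miss an excess. Even without pain, z at 33 per arm is only 1.41 on the assumed rates.
- *The effect collapses from fourfold to almost nothing.* On the assumed rates the risk ratio does fall from 4.0 to 1.44 or 1.20, but the planned measure is the risk difference, which loses 15% or 30% of its size.
- *Persisting pain is unrelated to allocation.* The trial expects the arms to differ in recovery and measures KOOS Pain. If rehabilitation changes pain, some of these events are genuine effects.

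It may also be said that grading against baseline is detail for the fuller protocol, and that the ambulatory-cure qualifier narrows the item. The qualifier does not separate residual from new pain, and the objection here is to a definition the article states, not to one it omits.

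**Conclusion.** The point holds in a limited form. As written, unresolved entry pain can be counted as an adverse event and reported as a complication, and this conflicts with the narrower definition in Materials and methods. If the wider definition is used as one any-event rate, the planned risk difference shrinks by the factor (1 − b) and its variance rises. On assumed rates of 3% v 12% and b of 15% to 30%, the difference falls from 9.0 to 7.65 or 6.3 points and power at 63 per arm from about 49% to 18% or 11%.

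This rests on pooling, on equal and independent background pain in both arms, and on rates the article does not give. The share of patients enrolled for pain is also unknown, and the inclusion list does not say whether pain and instability are alternatives. The primary range-of-motion endpoint and its sample size are unaffected.

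**What to change.** 1. Reconcile Materials and methods with Interim analysis into one definition of a complication, and use it for both the secondary hypothesis and the interim report.
2. Count pain as an adverse event only when it is new or worse than the patient's preoperative state, for example against the baseline KOOS Pain score, which is already collected.
3. Report structural and serious events (fixation failure or displacement, stress fracture, non-union, deep infection) separately from pain and other ambulatory events, both in the similarity comparison and to the interim board. Stress fracture needs explicit mention: it is a named complication in Materials and methods but is absent from the serious adverse event list, so relying on that list alone would drop it.

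Residual pain stays visible on its own line and in KOOS Pain, so an effect of rehabilitation on pain is not lost. The cost is protocol wording only, with no new data. The downside is fewer events in the main complication comparison, so its estimate will rest on small counts, and this should be said when it is reported.

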### Trial schedule

Approval for the study was sought in the autumn of 2022. Patient recruitment will start in the spring of 2024. The study will document short-term recovery and the planned follow-up will be 1 year. The number of operations will be collected until the spring of 2025. Follow-up control visits will take place until the spring of 2026.

After the 1-year follow-up, the results of the trial will be disseminated in a major peer-reviewed orthopaedic publication.
